### Objectives

In this study, we plan to collect clinically relevant data from patients in a real-world setting. The primary objective of this study is to evaluate the efficacy and safety of TCMIB treatment at 16 weeks in patients with moderate to severe AD, and the secondary objective is to analyze data on the involvement of TCM in the diagnosis, treatment, constitutional regulation, and prevention of relapse in AD so as to provide methodological insights to obtain high-quality evidence and inform future in-depth research on AD treatment. The findings are expected to provide further evidence for standardizing TCMIB regimens in the treatment of AD.

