## Methods

### Study Design

This is a multicenter, prospective, real-world study that will be conducted at 28 hospitals participating in the National Clinical Research Center for Skin and Immune Diseases Real-World Big Data Collection Platform from October 2024 to September 2028. The hospitals are listed in Table S1 in Multimedia Appendix 1. On the basis of the “disease-syndrome” classification framework, patients will be assigned to 7 groups according to their specific clinical presentations (n=500 per group): heat accumulation in the heart and spleen pattern (group A), heart fire with spleen deficiency pattern (group B), spleen deficiency with dampness pattern (group C), wind heat and dampness pattern (group D), spleen deficiency with blood dryness pattern (group E), spleen and kidney yang deficiency pattern (group F), and other patterns (group G). Patients in all groups will undergo a 16-week treatment phase and then a 36-week follow-up period. Baseline is defined as the time of enrollment (week 0) prior to the initiation of any treatment. Assessments will be conducted at baseline, every 2 weeks until week 16, and then every 4 weeks until week 52. The flowchart of this study is shown in Figure 1.

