### Treatment Plan

The treatment plans of patients included in the study are formulated in accordance with the expert consensus on TCM diagnosis and treatment of AD [22] and the guidelines for diagnosis and treatment of AD in TCM [21]. Patients in groups A to F will receive both TCM and biologic treatment (TCMIB groups), whereas patients in group G will receive biologic treatment only. TCM prescriptions include Sanxin Daochi decoction, Peitu Qingxin decoction, Xiao’er Huashi decoction, Shenling Baizhu powder, Xiaofeng powder, Jianpi Runfu decoction, Zhenwu decoction, and Wuling powder. All TCM prescriptions are administered as decoctions for oral use. The standard dosage is 1 dose per day, which is decocted in water and divided into 2 warm servings of 200 mL each. Dermatologists are permitted to individualize the base prescriptions according to each patient’s specific pattern differentiation. The biologic agent used in this study is dupilumab. The dosing regimen follows the expert consensus for dupilumab in the treatment of AD [10]: an initial dose of 600 mg (administered as two 300-mg subcutaneous injections) with a maintenance dose of 300 mg subcutaneously every 2 weeks. Patients in all 7 groups will undergo a 16-week treatment phase and then a 36-week follow-up period. Detailed treatment regimens are provided in Table S2 in Multimedia Appendix 1.

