### Outcomes

#### Primary Outcome

The eczema area and severity index (EASI) is one of the most widely used severity scales for assessing AD skin lesions, quantifying the severity of AD based on the area of involvement and the intensity of 4 clinical signs (erythema, edema or papulation, excoriation, and lichenification) in each body region [23]. The EASI score ranges from 0 to 72, with a higher score indicating a more severe disease condition. In this study, achieving an improvement of 75% or more in the EASI at week 16 from baseline (ie, EASI75) is designated as the primary outcome, calculated using the formula [(EASI at baseline – EASI at week *t*)/EASI at baseline] × 100%. The score will be evaluated at baseline, at every visit during the 16-week treatment period, and throughout the 36-week follow-up.

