### Safety Assessment

In this study, safety assessment will encompass monitoring of vital signs, recording of concomitant medications, physical examination, and recording of all adverse events (AEs) and serious AEs (SAEs). Vital signs, concomitant medications, AEs, and SAEs will be monitored at baseline, throughout the treatment period, and at week 52, whereas physical examinations will be performed at baseline, week 16, and week 52. A comprehensive study schedule is provided in Table S3 in Multimedia Appendix 1.

In this study, an AE is defined as any untoward medical occurrence in a patient following the initiation of treatment, which includes the presence or worsening of any syndrome, symptom, or disease. An SAE refers to any event occurring during the study that results in any of the following outcomes: hospitalization, prolongation of existing hospitalization, disability, inability to work, congenital anomaly, life-threatening condition, or death. Throughout the treatment period, the dermatologists will closely monitor the patients’ conditions. When AEs occur, the dermatologists will provide appropriate care based on the clinical presentation and will document relevant details, including the onset date, severity, relationship to study therapy, and resolution date of each event. All AEs will be monitored and followed up on until they are alleviated or properly resolved. Participants with AEs can withdraw from the study immediately and will receive appropriate medical management without cost. All AEs and SAEs will be reported in accordance with relevant regulatory requirements.

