### Data Collection and Management

We have designed a standardized case report form (CRF) for data collection. The CRF comprises the following sections: (1) demographic data, including age, gender, and educational level; (2) vital signs and physical examination, including blood pressure, pulse, height, and weight; (3) medical history, including past medical history, comorbidities, family history, and allergy history; (4) lifestyle habits (tobacco smoking and alcohol consumption); (5) AD assessments from baseline to week 52, including EASI, BSA, IGA, DLQI, NRS, POEM, ADCT, and TCM symptom scale; and (6) previous and current medications and AEs.

The aforementioned information will be collected by well-trained and experienced assessors through face-to-face interviews and subsequently documented in the CRFs. All CRFs will be verified by specialized personnel to preserve the integrity and accuracy of the information. CRF data will be uploaded to the National Clinical Research Center for Skin and Immune Diseases Real-World Big Data Collection Platform. Medical records will be retained at each study site in both paper and electronic formats. All data will be anonymized by removing any personally identifiable information that could directly reveal participant identities.

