### Statistical Analysis

This study will use the SAS software (version 9.4; SAS Institute) for statistical analysis. The reasons for missing data will be analyzed, and the multiple imputation method will be used for data completion. Statistical description and analysis will be performed on demographic characteristics and efficacy evaluation data. Quantitative variables following a normal distribution will be described using means and SDs and analyzed using either the 2-tailed *t* test or 2-tailed paired *t* test. Skew-distributed quantitative variables will be summarized as medians and IQRs and analyzed using the Wilcoxon rank-sum test. The quantitative variables of repeated measurement will be analyzed via repeated-measure ANOVA. Qualitative variables will be expressed as frequencies and percentages. The comparison between groups for categorical data will be conducted using the chi-square test, whereas repeated-measurement categorical data will be analyzed using the generalized estimating equations method. Generalized estimating equations models will be fitted with achievement of EASI75 response at each visit as the dependent variable and treatment regimen as the independent variable, adjusted for demographic characteristics (age and sex), medical history (family history and comorbidities), baseline disease severity (EASI, BSA, and IGA), and lifestyle factors (smoking and drinking). The working correlation structure will be selected based on the minimum quasi-likelihood under the independence model criterion. In addition, subgroup analyses will be performed stratified by age, sex, and disease severity. In this study, a *P* value below .05 will be considered statistically significant.

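### As printed, the adjusted EASI75 GEE has no visit or regimen-by-visit term, so its single regimen coefficient would blend on- and off-treatment visits and not estimate the adjusted week-16 effect

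*Protocol article*

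**What the plan says.** The Primary Outcome section sets EASI75 at week 16 as the primary outcome and adds: "The score will be evaluated at baseline, at every visit during the 16-week treatment period, and throughout the 36-week follow-up". The Study Design section gives the timetable: "Assessments will be conducted at baseline, every 2 weeks until week 16, and then every 4 weeks until week 52". The Treatment Plan section separates the two periods: "Patients in all 7 groups will undergo a 16-week treatment phase and then a 36-week follow-up period".

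The Statistical Analysis section then describes the adjusted model. Its outcome and exposure are given as "achievement of EASI75 response at each visit as the dependent variable and treatment regimen as the independent variable". The method is GEE, and the working correlation is to be chosen by the quasi-likelihood information criterion. The covariates are listed by name: the model is "adjusted for demographic characteristics (age and sex), medical history (family history and comorbidities), baseline disease severity (EASI, BSA, and IGA"; smoking and drinking complete the list. Neither visit nor a regimen-by-visit interaction appears. The other between-group method given for categorical outcomes is the chi-square test, which is unadjusted.

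**The concern.** Regimens are not randomised, and the Discussion acknowledges the risk of bias and unmeasured confounding. An adjusted estimate therefore matters here, and the GEE is the only one named for EASI75. The section is specific about it: outcome, exposure, covariates and correlation rule are all given. If it is fitted as written, every visit contributes to one regimen coefficient, and no adjusted estimate is tied to the primary time point.

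The blend also serves the longer-term question poorly. The secondary objective covers "constitutional regulation, and prevention of relapse in AD", which concerns what happens after week 16. A coefficient that mixes the two periods answers neither question cleanly, and the same value can arise from quite different time courses.

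**Working it through.** **Plan's own figure.** Inputs from Sample Size: p1 = 0.57, p2 = 0.70, two-sided alpha 0.01, power 0.90, dropout 15%. The printed formula gives (2.576 + 1.282)² × (0.57 × 0.43 + 0.70 × 0.30) / 0.13² = 400.7, rounded up to 401. Then 401 / 0.85 = 472 per group, as stated. This calculation concerns week 16 only.

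**Visits.** Weeks 2, 4, …, 16 give 8 on treatment. Weeks 20, 24, …, 52 give 9 after treatment. Of 17 records per complete patient, 9/17 = 53% are post-treatment and 1/17 = 6% is week 16.

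**Week-16 odds ratio.** (0.70/0.30) / (0.57/0.43) = 1.76.

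**What the printed model estimates.** With an independence working correlation, complete data, regimen as two levels (A–F v G) and covariates ignored, a GEE without visit terms estimates the odds ratio of the mean response over the 17 visits. The response at visits other than week 16 is assumed, with 45% in group G after week 16.

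- Flat effect (70% v 57% at all 8 treatment visits), none kept: group G (8 × 0.57 + 9 × 0.45)/17 = 0.506; TCMIB (8 × 0.70 + 9 × 0.45)/17 = 0.568; OR 1.28.
- Linear build-up (0.70k/8 v 0.57k/8, k = 1 to 8, so the multipliers k/8 sum to 4.5), none kept: group G (4.5 × 0.57 + 4.05)/17 = 0.389; TCMIB (4.5 × 0.70 + 4.05)/17 = 0.424; OR 1.15.
- Flat effect, all 13 points kept (58% v 45% after week 16): TCMIB (5.60 + 5.22)/17 = 0.636 v 0.506; OR 1.71.
- Linear build-up, all 13 points kept: TCMIB (3.15 + 5.22)/17 = 0.492 v 0.389; OR 1.52.

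For the flat effect with none kept, a group G response of 30% or 60% after week 16 in place of 45% gives 1.28 or 1.30.

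**The error can also go upward.** Take another assumed course: group G rises from 10% to 57% by week 16, then falls from 55% to 30%. If the log odds ratio builds up to week 16 and then doubles in follow-up, the pooled OR is 2.03 against 1.76 at week 16. If there is no effect through week 16 and one only afterwards (OR 1.76 at each follow-up visit), the pooled OR is 1.34 although the week-16 OR is 1.00.

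**Partial remedies, same assumptions** (3000 v 500 patients, 45% after week 16, none kept):

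| Model | Flat | Linear |
|---|---|---|
| No visit terms, 17 visits | 1.28 | 1.15 |
| Visit main effects only, 17 visits | 1.30 | 1.17 |
| Visits to week 16, no visit terms | 1.76 | 1.38 |
| Visits to week 16, visit main effects | 1.76 | 1.46 |
| Visit and regimen-by-visit, week-16 contrast | 1.76 | 1.76 |

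Visit main effects alone do not help. Stopping at week 16 recovers the effect only if it is constant over treatment.

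**The case against.** The strongest reply is that this is a condensed article. Time terms and the reported contrast are routine content of a full analysis plan, the adjustment list can be read as confounders only, and nothing says that visit is excluded or that one coefficient will be reported. It is right that the full plan may contain these terms, so the point is limited to the model as printed. But the article does set out this model's terms, and those terms, followed as written, do not give the adjusted week-16 effect.

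The 17-visit window is also an inference. The text could mean treatment visits only, or one model per visit. The EASI schedule runs through follow-up, and choosing a working correlation implies repeated visits in one model, so a single pooled model is the likelier reading. It is not an explicit statement. A treatment-phase model would still miss week 16 if the effect builds up.

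The size is illustrative. Only 57% and 70% at week 16 come from the protocol, and the real weights depend on the working correlation and missing data.

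A reader might go further and infer that differences in weeks 20 to 52 cannot be interpreted, because "concomitant medications, AEs, and SAEs will be monitored at baseline, throughout the treatment period, and at week 52" covers one of the nine follow-up visits. The documents do not support that. The case report form has a section for "previous and current medications and AEs", a week-52 entry could cover the interval, the full schedule (Table S3) is not shown, and no later systemic therapy is described. Nor does the June 2028 analysis start show a defect: a patient enrolled on 31 January 2028 reaches week 16 on 22 May 2028, and no analysis of incomplete follow-up is stated.

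**Conclusion.** The point holds for the adjusted EASI75 model as printed. On the likelier reading, its regimen coefficient is a weighted average over 8 on-treatment and 9 post-treatment visits and is not the adjusted effect at the primary time point. Under the assumed curves, a week-16 OR of 1.76 would appear as 1.15 to 1.28 if nothing is kept after treatment and as 1.52 to 1.71 if all 13 points are kept. It would appear as more than 1.76 if the effect grows enough in follow-up. These figures are not bounds, and neither direction can be presumed.

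A reader might infer that the primary result itself is compromised. It is not: the chi-square test can still compare week-16 response, though without adjustment, and the sample size of 472 before rounding up to 500 reproduces. What is missing as printed is an adjusted estimate at week 16. Confidence is moderate, because the full plan is not shown.

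**What to change.** In Statistical Analysis, add visit (categorical) and regimen-by-visit terms to the EASI75 GEE. Name the adjusted regimen contrast at week 16 as the main adjusted result, and report weeks 20 to 52 as separate contrasts. State which visits enter the model. If the full plan already does this, one sentence in the article saying so is enough.

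The change needs one or two sentences and no new data. The price is precision: the week-16 contrast will have a wider interval than a coefficient pooled over 17 visits. Restricting the model to visits through week 16 is simpler but relies on a constant effect, so the week-16 contrast is preferable.

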### Sample Size

The improvement of 75% or more in the eczema area and severity index (EASI75) response rate at week 16 will be adopted as the primary efficacy outcome in this study. On the basis of prior data [29], a 57% response rate will be assumed in patients with biologic treatment (group G; *p*_1_= 0.57), and a 70% response rate will be assumed for the TCMIB group (groups A-F; *p*_2_=0.70). A 2-sided significance level (α) of .01 and a statistical power (1 − β) of 0.90 are specified. According to the sample size calculation formula n = (μ_α/2_ + μ_β_)^2^ × [*p*_1_(1 − *p*_1_) + *p*_2_(1 − *p*_2_)]/(*p*_2_ − *p*_1_)^2^, and considering a 15% dropout rate, at least 472 patients should be enrolled in each group. The final sample size is determined to be 500 patients per group. A total of at least 3500 participants are planned to be enrolled. Additionally, each participating hospital is expected to recruit a minimum of 100 patients, with at least 10 patients in each of the 7 treatment groups.

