This protocol outlines the design of a prospective, multicenter, large-scale observational study that provides a real-world setting to explore the role of TCM in the diagnosis and treatment of, constitutional regulation of, and prevention of relapse in AD. To our knowledge, this is the first multicenter observational study in China to enroll at least 3500 patients with moderate to severe AD. The study will analyze the demographic and TCM-specific characteristic profiles of the AD cohort and identify optimal TCMIB therapeutic strategies through long-term observation. Furthermore, it will provide critical data on the effectiveness and safety of a 16-week TCMIB intervention and explore whether this treatment yields additional clinical benefits. Beyond these immediate goals, the creation of a shared clinical database is expected to provide substantial data support for subsequent TCM research, ultimately contributing to the progression of AD clinical research and management.

There are some limitations to this study. First, patient-reported outcomes such as NRS for pruritus and POEM are inherently subjective and may be biased by interindividual differences in symptom perception thresholds. Second, the total period of this study is 52 weeks (including a 16-week treatment period and a 36-week follow-up period). For various reasons, some patients may have difficulty completing the whole study cycle, resulting in loss to follow-up. Third, as this is a real-world study, patients’ treatment regimens are not randomly assigned, making the results susceptible to certain biases. The potential influence of unmeasured confounding factors on the study results cannot be excluded, which poses challenges to causal inference. Fourth, while external TCM treatment methods (eg, topical Chinese medicine and acupuncture) have all shown therapeutic promise in AD [33-35], this study is restricted to oral TCM formulations. This focus limits the comprehensiveness of the assessment regarding the full therapeutic potential of TCM for AD.

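### Hospital is missing from the stated covariates of the EASI75 model in a non-randomised 28-hospital study, so remaining hospital differences can bias the comparison of groups A–F with group G

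*Protocol article*

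**What the plan says.** Study Design describes a "multicenter, prospective, real-world study that will be conducted at 28 hospitals". Patients enter one of seven groups by TCM pattern, with 500 planned per group. Under Treatment Plan, groups A to F receive TCM with dupilumab, "whereas patients in group G will receive biologic treatment only". The Discussion concedes that "patients’ treatment regimens are not randomly assigned, making the results susceptible to certain biases".

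The rule on recruitment by hospital is in Sample Size: "each participating hospital is expected to recruit a minimum of 100 patients, with at least 10 patients in each of the 7 treatment groups". No maximum per hospital and no target mix is given.

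Statistical Analysis names the covariates of the EASI75 GEE. The model is "adjusted for demographic characteristics (age and sex), medical history (family history and comorbidities), baseline disease severity", the last measured by EASI, BSA and IGA, followed by smoking and drinking. The working correlation structure is chosen by a quasi-likelihood information criterion. The other between-group methods named are the t test, the Wilcoxon rank-sum test and the chi-square test, none of which takes a covariate, and repeated-measures ANOVA. Subgroups are age, sex and severity. Hospital does not appear in the section.

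**The concern.** Without randomisation, hospital can be related to both group and outcome. The group mix may differ between hospitals because only floors are set. The EASI75 rate may differ because of referral pattern, background care or rating habits. If both differ, part of any A–F versus G difference is a difference between hospitals.

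The listed covariates remove only what they measure. Choosing a working correlation structure deals with dependence between observations, not with confounding by hospital. The Discussion's caveat is about unmeasured confounders, whereas hospital is known for every patient.

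At stake is whether a difference around the planned 13 points could be read as the contribution of TCM.

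**Working it through.** **Inputs from the article.** 28 hospitals; 500 per group, so 3000 in A–F and 500 in G; at least 100 patients per hospital and 10 per group; assumed response 57% (G) and 70% (A–F); two-sided alpha .01; power 0.90; dropout 15%.

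**Input assumed.** D is the gap in EASI75 rate between two sets of hospitals that remains after the listed adjustment, the same in every treatment group. The article gives no value. I use 5, 10, 15 and 20 points.

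1. **The plan's own figure.** (2.576 + 1.282)² × [0.57 × 0.43 + 0.70 × 0.30] / 0.13² = 400.7, so 401; 401 / 0.85 = 472. The stated 472 reproduces and is not in dispute. At 15% dropout, 500 gives 425 evaluable and 3000 gives 2550.

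2. **What the floors secure.** 28 × 10 = 280 of 500 per group. The other 220 may come from anywhere.

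3. **Bias formula.** Let s_G and s_T be the shares of G and of A–F treated in the lower-response hospitals. Leaving hospital out adds (s_G − s_T) × D to the difference A–F minus G. If the hospitals rich in G respond better, the sign reverses.

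4. **Ceiling on the weight.** With the floors met and 500 per group, k hospitals hold at most 500 − 10 × (28 − k) of G, a share of 0.44 + 0.02k. They hold at least 60k of the 3000 in A–F, a share of 0.02k. The weight cannot exceed 0.44.

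5. **Layouts.**
 - Very uneven, all hospitals of size 3500 / 28 = 125: four with 65 G patients and 24 with 10. Weight = 260/500 − 240/3000 = 0.52 − 0.08 = 0.44, the ceiling.
 - One hospital with 230 of G, the rest with 10 each, A–F spread evenly: 230/500 − 1/28 = 0.424.
 - Mild: 14 hospitals with 25 G patients and 14 with about 10.7. Weight = 350/500 − 1400/3000 = 0.233.

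6. **Bias, and chance of a significant result with no true effect.** The last two columns are for the very uneven layout, by normal approximation, 2550 versus 425, G at 57%.

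| D (points) | Bias, mild | Bias, very uneven | Share of 13 points (very uneven) | P(significant), .05 | P(significant), .01 |
|---|---|---|---|---|---|
| 5 | 1.2 | 2.2 | 17% | 0.14 | 0.04 |
| 10 | 2.3 | 4.4 | 34% | 0.40 | 0.19 |
| 15 | 3.5 | 6.6 | 51% | 0.72 | 0.49 |
| 20 | 4.7 | 8.8 | 68% | 0.93 | 0.80 |

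7. **Price of comparing within hospital.** Efficiency = Σ n_G n_T / (n_G + n_T) over hospitals, divided by the unstratified value. For A–F versus G the latter is 500 × 3000 / 3500 = 428.6.
 - Very uneven: 4 × 65 × 60/125 + 24 × 10 × 115/125 = 345.6, or 81%. Power at alpha .01 goes from 0.996 to 0.982.
 - One dominant hospital: about 320, or 75%.
 - One TCM group versus G, very uneven: 4 × 650/75 + 24 × (10 × 19.17/29.17) = 192.4, against 250, or 77%. Power at alpha .01 goes from 0.915 to 0.812.
 - Equal mix: no loss.

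**The case against.** The strongest reply is that this is a condensed article, that handling of centre is often left to an analysis plan, and that the covariate list is not said to be exhaustive. This has weight, but the article does not leave the model open. It names the covariates one by one and omits hospital, so an analyst who follows it would not adjust for hospital.

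The second reply is that much is already controlled. The model adjusts for baseline severity, age, sex, comorbidities and lifestyle. Pattern diagnosis follows one named standard, the dupilumab regimen is common to all groups, and the case report form is standardised and verified. This stands, and it is why D must be read as the gap left after adjustment. It may be small.

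Third, the very uneven layout is the ceiling that the floors allow, not a forecast. The mild layout is a second reference point, and no enrolment mix is published.

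A reader might also infer more than the text supports:

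- **That the contrast is biased.** Bias needs both the mix and the adjusted response to differ by hospital. Neither is documented.
- **That treating dermatologists score EASI unblinded.** The article does not say who scores EASI or whether scorers are blinded. Data Collection and Management refers to trained assessors, and dermatologists are named as raters for BSA only.
- **That the floor of 10 was set to allow within-hospital comparison.** It would help such a comparison, but no reason for it is given.
- **That tailoring of prescriptions is itself a confounder.** "Dermatologists are permitted to individualize the base prescriptions" concerns the TCM regimen, which only A–F receive. Local variation in it is variation in the treatment being studied.

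**Conclusion.** The point holds as a possible bias from a stated modelling choice. Hospital is absent from an explicit covariate list, and nothing else in the article allows for it. With 500 per group and the floors met, the bias is at most 0.44 × D. At D = 10 it is about 2.3 points in the mild layout and 4.4 in the most uneven one, which is 18% to 34% of the planned 13 points. These sizes rest on an assumed D, on hospital effects that are the same in all groups, and on assumed layouts.

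It would be wrong to infer that adjusting for hospital makes the contrast causal. Group G consists of the remaining TCM patterns, so pattern and treatment stay confounded within every hospital.

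**What to change.** - Add hospital as a fixed effect (28 levels) to the EASI75 GEE.
- For the secondary between-group comparisons, replace the unadjusted t, Wilcoxon and chi-square tests with hospital-adjusted or hospital-stratified methods.
- As a sensitivity analysis, use a robust variance clustered by hospital, with a small-sample correction for 28 clusters.
- State in the limitations that this does not separate TCM pattern from treatment.

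The cost is 27 parameters on about 3500 patients, a change of method for the secondary tests, and the loss of precision shown above if the mix is uneven. That loss is modest for A–F pooled versus G. It is more noticeable for one TCM group versus G, where power falls to about 0.81 in the most uneven layout. No new data should be needed, assuming that the shared platform identifies the recruiting hospital. Recruitment is planned to end in January 2028 and analysis to start in June 2028, so the change can be made before the analysis begins.

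### The only adjusted EASI75 model controls severity through clinician ratings alone and leaves out baseline itch and patient-reported burden, so some measured confounding may remain

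*Protocol article*

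**What the plan says.** **Grouping and regimen.** Under Study Design, "patients will be assigned to 7 groups according to their specific clinical presentations". Under Treatment Plan, groups A to F receive TCM with dupilumab and group G receives dupilumab alone. A patient's presentation therefore decides whether TCM is given.

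**Adjusted model.** Under Statistical Analysis, the GEE takes "achievement of EASI75 response at each visit as the dependent variable and treatment regimen as the independent variable". It is "adjusted for demographic characteristics (age and sex), medical history (family history and comorbidities"), and then for "baseline disease severity (EASI, BSA, and IGA), and lifestyle factors (smoking and drinking"). The list is written out item by item, with no wording that marks the items as examples.

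**Other between-group test.** The same section says: "The comparison between groups for categorical data will be conducted using the chi-square test". That test has no covariates. The section does not say which of the two is the primary analysis of week-16 EASI75.

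**Data held.** Under Data Collection and Management, the case report form contains "AD assessments from baseline to week 52, including EASI, BSA, IGA, DLQI, NRS, POEM, ADCT, and TCM symptom scale". The sections on the individual scales schedule NRS, POEM, ADCT and DLQI at baseline. The form also holds "medical history, including past medical history, comorbidities, family history, and allergy history" and "vital signs and physical examination, including blood pressure, pulse, height, and weight".

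**The concern.** In a non-randomised comparison the covariate list carries whatever control of confounding the analysis has. Here the three severity covariates describe what the clinician sees. EASI scores area and four skin signs, BSA scores extent, and IGA is a global judgement of erythema, infiltration and papulation. None records how strongly the patient itches, how the patient sleeps, or how well controlled the disease feels.

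Those features belong to the clinical presentation. The TCM Symptom Scale section lists itch severity in the local part and sleep quality in the systemic part. It calls the scale nonquantitative, so it is not an easy covariate. NRS and POEM cover the same ground as numeric scores. If they differ between A–F and G, and predict EASI75 beyond EASI, BSA and IGA, part of the estimated regimen effect would be a baseline difference that the study had measured and not used. The limitations paragraph in the Discussion concedes non-random treatment and unmeasured confounders, but does not mention measured variables left out of the model.

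**Working it through.** **1. The plan's own figure.** Inputs from Sample Size: response 0.57 in G and 0.70 in A–F, two-sided α 0.01, power 0.90, dropout 15%.

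n = (2.576 + 1.282)² × (0.57×0.43 + 0.70×0.30) / 0.13² = 400.7, so 401. Then 401/0.85 = 471.8, so 472. The stated 472 is reproduced, and this point does not alter it.

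**2. Covariates against data collected at baseline.**

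| Variable | Collected | In the GEE | Documented link to grouping |
|---|---|---|---|
| EASI, BSA, IGA | yes | yes | visible signs |
| NRS itch | yes | no | itch severity is in the TCM assessment |
| POEM | yes | no | covers itch and sleep, both in the TCM assessment |
| ADCT | yes | no | its items include itch and sleep |
| DLQI | yes | no | indirect, through symptoms |
| Allergy history | yes | no (comorbidities are in) | none stated |
| Weight | yes | no | none stated |

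The omission of itch and patient-reported burden is confirmed. These are also the variables with a documented, if indirect, link to grouping.

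**3. How large the bias could be.** The article gives neither the imbalance nor the association with response, so both are assumed:

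- no true regimen effect, and 57% response;
- omitted factors together differ by 0.1 to 0.3 SD between A–F and G;
- log-odds of response of 0.2 to 0.4 per SD, given the listed covariates.

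Bias on the logit scale ≈ imbalance × log-odds per SD. This is 0.1×0.2 = 0.02 at the low end and 0.3×0.4 = 0.12 at the high end. The spurious odds ratio is exp(0.02) = 1.02 to exp(0.12) = 1.13. From 57%, that is 0.5 to 2.9 percentage points, or about 4% to 22% of the planned 13 points (0.5/13 and 2.9/13).

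Evaluable patients after 15% dropout: G 500×0.85 = 425; A–F 6×500×0.85 = 2550; total 2975.

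SE of the log odds ratio = √[1/(425×0.2451) + 1/(2550×0.2451)] = √(0.0096 + 0.0016) = 0.106, where 0.2451 = 0.57×0.43.

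Type I error = P(|Z + bias/SE| > critical value):

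| Logit bias | bias/SE | at .05 | at .01 |
|---|---|---|---|
| 0.02 | 0.19 | about 5% | about 1% |
| 0.12 | 1.13 | about 20.5% | about 7.5% |

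The .05 column matches the level in the Statistical Analysis section. The .01 column matches the level used for sample size.

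**4. A second illustration.** Take one omitted binary covariate, with bias = prevalence imbalance × effect on response. An imbalance of 5 to 30 points and an effect of 5 to 20 points give a bias of 0.25 to 6.0 points, or 2% to 46% of the planned 13. With 425 and 2550 patients and no true effect, the false-positive rate at .05 runs from 0.051 to 0.64; it is 0.067 at 10×10 points and 0.121 at 20×10.

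Both ranges follow from their assumptions. Neither estimates what this study will show, and the direction of any bias is unknown.

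**The case against.** The plan already names nine covariates, including the baseline value of the outcome scale and two further severity measures. A longer list could be called a matter of preference, and an analysis plan that is not shown may refine it. This stands in part. The article contains no contradiction here, but it does spell out a list that reads as complete and leaves out scores it collects.

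Four stronger readings are tempting, and the documents do not support them.

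- **That confounding is present.** A confounder must differ between A–F and G and must predict EASI75 after adjustment for EASI, BSA, IGA and comorbidities. The article shows neither. The pattern criteria come from an external standard that is not reproduced, and EASI already scores excoriation, which may carry some of the itch information. Only the possibility can be claimed.
- **That weight, allergy history and educational level belong on the same footing.** Nothing in the article links them to TCM pattern. Weight would at most be prognostic, and comorbidities may already capture much of the allergic history, since the Introduction names food allergy, asthma and allergic rhinitis as associated conditions.
- **That the primary analysis is affected.** The GEE is not labelled primary. If the chi-square test is primary, a better GEE leaves the main result untouched. This does not remove the point, because the GEE is the only adjusted EASI75 model described, but the fix must also say which analysis is used.
- **That a fuller list would remove the confounding.** Pattern determines regimen, so pattern and treatment cannot be separated by any covariate.

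**Conclusion.** The point holds as a modest, specific weakness. The only adjusted EASI75 model controls severity through clinician ratings alone. It omits baseline itch and patient-reported burden, which are collected and plausibly related to the presentation that sets the regimen. Measured confounding may remain, and its size cannot be computed from the documents.

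Under the assumptions of step 3 it ranges from negligible (0.5 points, type I error about 5% at .05) to material for inference (2.9 points, about 20.5%). Even the upper end is less than a quarter of the planned 13-point difference. The wider figures in step 4 need a single omitted factor with both a large imbalance and a large effect. The case is strongest for NRS and POEM and weak for allergy history and weight.

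**What to change.** In the Statistical Analysis section:

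1. Add baseline NRS and one patient-reported score to the prespecified GEE covariates. POEM fits best because it covers itch and sleep; ADCT or DLQI would also serve.
2. State that this adjusted model, not the unadjusted chi-square test, gives the week-16 EASI75 comparison of A–F with G.
3. Report standardised mean differences by regimen for all baseline covariates, including the added ones, so that the reader can see whether imbalance exists.
4. Treat allergy history and weight or BMI as optional, in a sensitivity model.
5. State that confounding of TCM pattern with treatment remains whatever the covariate list.

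The cost is a few lines of text. The data are already on the case report form, and a few more degrees of freedom are negligible against about 2975 evaluable patients. Some collinearity among severity measures is to be expected; it affects the covariate coefficients more than the regimen effect. Analysis is planned to start in June 2028, so the list can still be fixed beforehand; added later, it would look driven by the results.
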